# Effect of Massage on treatment of preterm feeding intolerance: Study protocol for a randomized controlled trial

**DOI:** 10.1002/nop2.1733

**Published:** 2023-04-17

**Keywords:** feeding intolerance, massage, preterm infants

## Abstract

**Aim:**

To evaluate the effectiveness of massage on treating feeding intolerance (FI).

**Design:**

A randomized, controlled, prospective clinical trial.

**Methods:**

A total of 104 preterm infants whose gestational age between 28 and 34 weeks and birth weight between 1000 and 2000 g with diagnosis of FI were recruited. Participants were stratified by birth weight (1000–1499 g or 1500–2000 g) and randomized to either the intervention group, who will receive 7 days of massage, or the control group. The primary outcome is the time to reach full enteral nutrition. Secondary outcomes include duration of FI, change of body index, length of hospitalization, change of gastric residual volume, abdomen circumference and defecation measurement before and after 7 days of intervention.

**Results:**

Results of this study, which includes index on FI and physical development, have the potential to provide evidence that massage will alleviate symptoms of FI, and contribute to the long‐term positive outcome of preterm infants.

## BACKGROUND

1

Over 14.9 million babies are born prematurely across the world every year, and the number is still increasing (Heinonen et al., 2016). Due to immature gastrointestinal function, premature newborns especially those born before 34 weeks, are susceptible to feeding intolerance (FI) (Asadi et al., 2019), and its morbidity could achieve 70% (Ng et al., 2019). Currently, there is no universal definition of FI, the widely accepted one is the following: the gastric residual volume (GRV) was 50% greater than the last feeding volume, with abdominal distension or vomiting (Moore & Wilson, 2011).

FI could badly influence newborns' health. During the neonatal period, it may lead to malnutrition, delayed enteral nutrition, prolonged hospitalization, growth restriction and increase the risk of sepsis and serious gastrointestinal complications such as necrotizing enterocolitis (NEC) (Meister et al., 2019; Neu, 2007). Additionally, it may lead to long‐term negative outcomes such as visceral obesity, glucose intolerance, and increased risk of cardiovascular disease, negative neurodevelopmental outcomes in adulthood (Asadi et al., 2019). At present, treatment for FI includes breastfeeding, modifications in feeding regimes, use of probiotics or medicine, but effectiveness and safety of these methods remain controversial (Basu & Smith, 2020; Fanaro, 2012; Sukwuttichai et al., 2021), feeding intolerance (FI) is still a thorny issue affecting the prognosis of preterm infants. So it is important to find an effective way to cure FI, contributing to recovery of gastrointestinal function and improving long‐term health of preterm infants.

In recent years, massage therapy has been frequently used in neonatal wards for the prevention of FI. Studies have shown that massage could prevent gastric retention and abdominal distention in premature infants, and reduce the length of stay. In addition, massage could stimulate the digestive system and the vagus nerve in premature infants, potentially improving their physical growth (Diego et al., 2007; Heinonen et al., 2016; Tekgündüz et al., 2014). However, there is no consensus on the efficacy of massage in the treatment of FI.

## AIM

2

To determine the efficacy of massage in the therapy of FI, thus providing a new, safe and efficient method for the treatment of preterm FI.

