### Safety

3.9

As safety of massage has been proven in previous studies, our intervention would not induce any complications in most cases. And we took several measurements to avoid the occurrence of adverse events. The strength of massage was controlled so that the baby's skin changes just from pink to white. During massage, the massager paid close attention to the ECG monitor. Massage was suspended when the baby's vital signs (such as respiratory rate, heart rate and oxygen saturation) were not stable (Diego et al., 2009; Indrio et al., 2011), or the baby began to cry, urinate or defecate. Massager would continue massage only when the baby returns to a stable condition.

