#### Primary outcome

3.10.1

The time (day) from initiation of enteral nutrition to total enteral nutrition, which is defined as a daily intake of ≥120 mL/Kg/day (Abdallah et al., 2013).

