## DISCUSSION

4

This article describes the methodology of a study designed on the effects of massage on the treatment of preterm FI. A total of 104 preterm infants will be included in this trial, they will be stratified according to their birth weight and then assigned to the massage group or control group randomly. Variables include index on FI and physical development will be recorded.

We combined abdominal massage and skin stroking in our trail. According to scientific literature, abdominal massage stimulates gastrointestinal peristalsis by increasing vagus nerve activity (Moyer et al., 2004). Additionally, it can affect abdominal pressure and have a mechanical and reactive impact on the intestines (Harrington & Haskvitz, 2006; Liu et al., 2005). Skin stroking may activate the baroreceptors and mechanoreceptors of the skin as well as the vagal efferent fibres that innervate the digestive system (Diego et al., 2005; Field, 2016). Consequently, we hypothesized that a combination of abdominal massage and skin stroking may be more effective than earlier interventions.

There were several studies investigating the benefits of massage, but low sample size and differences in the duration and frequency of massage in these studies were their limitations (Ghasemi et al., 2019; Shaeri et al., 2017; Soheila et al., 2013; Zaky Mohamed & Saied Ahmed, 2018). This study with accurate methodology, longer interventions and large sample size has the potential to give proof that preterm infant massage benefits in the recovery of gastrointestinal function and promotes growth and development if it is conducted successfully. Owing to the lack of research on the treatment of FI, it is anticipated that this study will fill a large gap in the literature.

Massage also has other advantages for preterm infants, such as promoting physical development, strengthening the immune system, reducing stress, and reducing the time of hospitalization (Niemi, 2017). So, this study may give a novel nursing practice for enhancing the long‐term outcomes of premature infants and could be widely used in neonatal wards.

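### The aim calls massage safe, but no safety event is among the stated outcomes or in the printed schedule, so the trial as printed would have no listed by-arm data to support that word

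*Protocol article*

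**What the plan says.** The aim in section 2 of the protocol article is to determine how well massage works as a therapy for FI, "thus providing a new, safe and efficient method for the treatment of preterm FI". Efficacy is what is to be determined; safety is part of what is expected to follow.

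Section 3.9 takes safety from outside the trial: "As safety of massage has been proven in previous studies, our intervention would not induce any complications in most cases". It then describes precautions: "Massage was suspended when the baby's vital signs (such as respiratory rate, heart rate and oxygen saturation) were not stable". Crying, urination and defecation also interrupt a session. The article does not say that interruptions are recorded.

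The primary outcome (section 3.10.1) is the time "from initiation of enteral nutrition to total enteral nutrition, which is defined as a daily intake of" at least 120 mL/kg. The secondary outcomes (section 3.10.2) are days with FI symptoms, growth, length of stay, and day 1 to day 7 changes in abdominal girth, gastric residual and stool frequency. Table 3 (section 3.11) schedules consent, baseline, feeding, symptom and growth items.

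On earlier evidence, section 1 says that "massage therapy has been frequently used in neonatal wards for the prevention of FI", and section 4 begins a sentence with "Owing to the lack of research on the treatment of FI".

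Safety oversight is mentioned in two places. Section 3.13 gives a Steering Committee the monitoring of patient safety, and the ethics section has the Ethics Committee review safety every 6 months. Death before total enteral nutrition is an exit criterion (Table 1). Infants who discontinue or deviate are left out of the analysis (section 3.11).

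**The concern.** The word *safe* describes a conclusion about harms, and the printed outcomes and schedule give no data from which to draw it. The infants already have FI, which section 1 says raises the risk of sepsis and NEC, and part of the intervention is massage of the abdomen. An imbalance in such events is the first thing a neonatal reader would look for. If the report follows the printed outcomes, it has no listed item from which to show one.

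The analysis set adds to the problem. An infant whose massage is stopped because of a complication could count as having discontinued and so disappear from the analysis. Section 4 says the method could come into wide use in neonatal wards, so an unsupported safety statement could be carried into practice.

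**Working it through.** **1. Outcomes and schedule against the aim.** Counting the printed items:

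| Place | Items | Safety events |
|---|---|---|
| Section 3.10.1 | time to total enteral nutrition | 0 |
| Section 3.10.2 | FI symptom days, growth, length of stay, day 1 to day 7 changes | 0 |
| Table 3 | 17 rows over T1 to T6 | 0 |

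NEC and sepsis appear in section 1 as risks of FI and in Table 1 as exclusions before recruitment. Neither is listed after randomisation. Death appears only as an exit criterion. Vomiting, distension and weight give indirect information on tolerability, but they are efficacy or growth measures here.

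**2. The basis given for safety.** Section 3.9 relies on earlier studies. Section 1 places the frequent use of massage in prevention, and section 4 says research on treatment is lacking. Section 4 also presents this regimen as a new combination (abdominal massage plus skin stroking) with longer interventions than before. The article's own account therefore gives limited reason to carry earlier safety findings over to this population and regimen.

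**3. What collection could show.** Inputs from section 3.4: 41 per group, and 52 per group after a 20% loss. The loss step reproduces: 41/(1 − 0.20) = 51.25, rounded up to 52, and 2 × 52 = 104. The base figure of 41 cannot be reproduced because no standard deviation is printed, but nothing here depends on it.

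With zero events in n infants, the exact upper limit is 1 − a^(1/n), where a = 0.025 for the two-sided 95% limit and a = 0.05 for the one-sided limit.

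| n | Two-sided 95% | One-sided 95% |
|---|---|---|
| 52 | 1 − 0.025^(1/52) = 6.8% | 1 − 0.05^(1/52) = 5.6% |
| 41 | 1 − 0.025^(1/41) = 8.6% | 1 − 0.05^(1/41) = 7.0% |

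The row for 52 applies if all randomised infants are reported. The row for 41 shows what remains if the full planned loss occurs.

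**4. Chance of seeing an event at all.** The article gives no event rates, so these are assumed. With 52 infants the chance of at least one event is 1 − (1 − p)^52: 41% for p = 1%, 65% for p = 2%, 93% for p = 5%. For a comparison of arms at assumed rates of 5% and 15%, power with 52 per group is about 40% (two-sided 0.05). Event data would therefore be descriptive, not a test of safety.

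**The case against.** The strongest reply is that the aim is efficacy. *Safe* stands in a consequence clause, the abstract gives effectiveness alone as the aim, and neither the abstract nor the discussion promises a safety analysis. This stands in part. A reader might infer that the trial sets out to demonstrate safety, and the text does not go that far. It does name safety as something the result will provide, and that is enough for the mismatch.

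The second reply is that absence from Table 3 does not prove that nothing is collected. This stands too. The article is condensed, the case report forms are not reproduced, and Table 3 is visibly incomplete: it has no row for length of stay or for days of gastric retention, both stated secondary outcomes. A reader might infer that no form records harms, or that the report could give no event counts at all. The article does not establish either. Deaths before total enteral nutrition must at least be identified, because they are an exit criterion. The committee reviews imply that some safety information is gathered, although no data item and no comparison by arm is named for them.

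Third, a reader might infer that earlier evidence excludes infants with FI altogether. The article says research on treatment is lacking, not that there is none, and section 3.8 cites studies as having validated safety. Their populations cannot be checked from the article.

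What remains is narrower but firm. The article prints an outcome list and a safety section, and neither names a safety event to be measured.

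**Conclusion.** The point holds as a mismatch within the article between the word *safe* in the aim and the outcomes and schedule it prints: no safety event among the outcomes and none in 17 schedule rows. Nothing listed would allow a safety statement by arm, and leaving out infants who discontinue or deviate weakens any such statement further. Even full collection with zero events in 52 infants would leave true rates up to about 6.8% compatible with the data (8.6% with 41), so *safe* is too strong either way.

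This is a should-fix. The primary outcome, the sample size and the efficacy analysis are not affected. The conclusion assumes that the printed outcome list is the one the report will follow. If the full protocol or the case report forms already define safety events, what remains is to list them as an outcome and moderate the aim.

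**What to change.** 1. Add a secondary safety outcome to section 3.10 and matching CRF2 items and Table 3 rows, for both arms, from day 1 of intervention to discharge (T6). Cover NEC, sepsis and death at least; the investigators should settle the list and the definitions.
2. Report counts by randomised arm with exact 95% confidence intervals. Include all randomised infants, so that the section 3.11 exclusion of those who discontinue or deviate does not apply to this outcome.
3. Record suspended sessions and their reasons in a separate log kept by the massager, with unstable vital signs kept apart from crying, urination and defecation. This should not go on CRF2: a field filled only for massaged infants would reveal allocation to the assessors, whom section 3.6 keeps unaware of it.
4. In section 2, replace *safe* with a statement that observed events will be described by arm with their confidence limits.

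The cost is a little more data entry, one descriptive table and a more modest claim, with no added infants or procedures. Recruitment began in April 2021, so some infants may already be discharged. Their events can be added only if hospital records hold them, which is an assumption, and past suspended sessions may not be recoverable. The report should state any such gap.

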## METHOD

3

### Study setting

3.1

This trial is conducted at a large neonatal treatment center of a tertiary‐level children's hospital, which is affiliated with one of the excellent medical universities in the country. It has a 250‐bed neonatal unit with an annual admission rate of about 8000 newborns over the past 2 years, which could assure a large number of research subjects.

### Study design

3.2

Following the Standard Protocol Items: Recommendations for Interventional Trials (Chan et al., 2013), the study protocol describes the design of a randomized, controlled, prospective clinical trial. Preterm infants whose gestational age between 28 and 34 weeks and birth weight between 1000 and 2000 g with the diagnosis of FI were involved in the study. They were stratified by birth weight (1000–1499 g or 1500–2000 g) and randomized to either the intervention group or the control group. Figure 1 shows the procedure of our study.

**FIGURE 1 nop21733-fig-0001:**
[figure not shown]
Procedure of study.

### Participants: Inclusion/exclusion criteria

3.3

Table 1 specifies the criteria for inclusion, exclusion, termination and exit criteria. Inclusion and exclusion criteria were defined according to previous literature (Baldassarre et al., 2019; Ng et al., 2018; Yakobson et al., 2020).

**TABLE 1 nop21733-tbl-0001:** Inclusion, exclusion, termination and exit criteria.

*Inclusion criteria*
Meet the FI diagnostic criteria
Admitted to the Neonatal Treatment Center of the Affiliated Children's Hospital of Chongqing Medical University within 24 h after birth
28 weeks ≤ gestational age ≤ 34 weeks, 1000 g ≤ birth weight ≤ 2000 g
In clinically stable condition
The neonate's guardians are willing to participate in this trial
*Exclusion criteria*
Apgar score less than 4 at 5 min
Neonates with skin disease, intestinal obstruction, sepsis, necrotizing enterocolitis, gastrointestinal malformation, congenital heart disease, central nervous system disorder, immune deficiency, or any other disease that may affect the ability to eat and normal growth before recruitment
Neonates who need surgery which requires general anaesthesia (except for ligation of patent ductus arteriosus) before the day of randomization
Neonates whose blood pressure is not stable (using dopamine <5 mg /kg/min is permitted)
Ventilator dependent or FiO_2_ (Fraction of inspired oxygen) > 40% on the day of randomization (continuous positive airway pressure, nasal intubation, oxygen mask are allowed)
Neonates who are diagnosed with Grade III or IV ventricular haemorrhage (IVH) on the day or before randomization
*Termination criteria*
Discharge in a stable condition with doctor's advice
*Exit criteria*
Death or discharge before achieving total enteral nutrition
Guardian request to withdraw from the trail

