### Data collection and management

3.11

Table 3 shows the schedule of evaluations. Data of each participant were collected on case report forms (CRFs) and then electronically recorded on a computer. CRF1 records participants' baseline information and it was filled in when neonates were included in the trial. CFR2, which includes information about the outcome of this trial, will be filled in during the trial and when neonates discharge with advice.

**TABLE 3 nop21733-tbl-0003:** Schedule of evaluations.

	Staff member	CRF	T1	T2	T3	T4	T5	T6
Symptom of FI	Neonatal assistant	CRF1	**×**					
Informed consent	Research assistant	CRF1	**×**					
Contact information	Research assistant	CRF1	**×**					
Sex	Neonatal physician	CRF1		**×**				
Gestational age	Neonatal physician	CRF1		**×**	**×**			
Mode of delivery	Neonatal physician	CRF1		**×**				
Apgar score	Neonatal physician	CRF1		**×**				
Maternal issues	Neonatal physician	CRF1		**×**				
Weight	Neonatal nurse	CRF2		**×**	**×**			**×**
Gastric residual volume	Neonatal nurse	CRF2				**×**	**×**	
Abdominal circumference	Neonatal nurse	CRF2				**×**	**×**	
Frequency of defecation	Neonatal physician	CRF2				**×**	**×**	
Length	Neonatal nurse	CRF2		**×**				**×**
Head circumference	Neonatal nurse	CRF2		**×**				**×**
Time to achieving total enteral nutrition	Neonatal physician	CRF2						**×**
Duration of abdominal distension	Neonatal physician	CRF2						**×**
Duration of vomiting	Neonatal physician	CRF2						**×**

*Note*: T1, screening; T2, baseline evaluation; T3 randomization; T4, day 1 of intervention; T5, day 7 of intervention; T6, discharge.

Once recorded, data are locked to prevent changes. Access to the data is limited to researchers directly involved with this trial. Data about participants who discontinue or deviate from intervention will not be included in statistical analysis.

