### Statistical analysis

3.12

After the data for the entire sample has been collected, it will be performed using SPSS 25.0 software package. Missing data will be forecasted and filled using multiple imputations. A logistic regression model will be used to adjust for multiple potential confounders plain. Measurement data obeying the normal distribution will be expressed as mean (standard deviation), and t‐test will be used for comparing between two groups. Non‐normally distributed variables will be expressed as median (interquartile range), and compared by the use of non‐parametric Wilcoxon–Mann–Whitney test. Classification data will be described as cases count (construct Proportional) and compared using the chi‐square test or non‐parametric Wilcoxon–Mann–Whitney test. The confidence interval will be set at 95%. *p* < 0.05 will be considered statistically significant.

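### Infants who die or are discharged before full enteral nutrition have no primary outcome value, and the exit, exclusion and imputation rules give no valid way to keep them in the randomised comparison

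*Protocol article*

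**What the plan says.** All places are in the protocol article.

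- **Primary outcome (3.10.1):** "The time (day) from initiation of enteral nutrition to total enteral nutrition", reached at an intake of at least 120 mL/kg/day. Table 3 has it recorded once, at discharge.
- **Exit criteria (Table 1, section 3.3):** "Death or discharge before achieving total enteral nutrition" and "Guardian request to withdraw from the trail".
- **Data collection and management (3.11):** "Data about participants who discontinue or deviate from intervention will not be included in statistical analysis".
- **Statistical analysis (3.12):** for normally distributed measurements a t-"test will be used for comparing between two groups". Non-normal variables "will be expressed as median (interquartile range), and compared by the use of" the Wilcoxon-Mann-Whitney test. Also, "Missing data will be forecasted and filled using multiple imputations".
- **Sample size (3.4):** a superiority comparison of two independent means, 28.3 against 33.5 days, 41 per group, raised to 52 for a 20% loss.

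The article describes no censoring, competing event or worst-rank rule. It does not say whether imputation covers infants who exit.

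**The concern.** The first exit criterion is defined by not reaching the primary endpoint. Both planned tests need a number of days for every infant in the comparison, and these infants have none. The text offers two routes. Leaving them out compares feeding time among those who succeeded, a subgroup formed after randomisation. Imputing them assigns a day of full feeding to infants who did not reach it under observation, and for an infant who died no such day exists.

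If massage changes how many infants reach full feeds, and those who do not are mainly the slow feeders, the arm that loses more of them looks faster. The background section links feeding intolerance to sepsis and necrotizing enterocolitis, so such a relation is plausible. The primary estimate and its p-value are at stake, and the error can go either way.

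**Working it through.** **1. The plan's own figures.** The loss step reproduces: 41 / (1 − 0.20) = 51.25, rounded up to 52 per group and 104 in total. The allowance is 0.20 × 104 = 20.8, so about 21 infants may lack a primary value. The 41 cannot be reproduced because no standard deviation is stated. From n = 2 × (σ(Zα + Zβ)/δ)², with δ = 33.5 − 28.3 = 5.2 and the stated Z values 1.64 + 0.84 = 2.48:

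σ = 5.2 × √(41/2) / 2.48 = 9.49 days.

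These Z values do not match the stated α of 0.025 and power of 0.9. With 1.96 + 1.28 the implied σ is 7.26. That mismatch is a separate matter. Here 9.49 serves only as a working value.

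**2. What happens to an infant without the endpoint.**

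| Situation | Exit criteria | Exclusion sentence (3.11) | Imputation sentence (3.12) |
|---|---|---|---|
| Dies or is discharged during the 7-day course, before full feeds | exits | plausibly excluded as having discontinued | not stated |
| Completes 7 days, later dies before full feeds | exits | not clearly covered | possible, but no feeding time exists |
| Completes 7 days, discharged before full feeds | exits | not clearly covered | possible, basis not stated |

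No row ends in a valid primary value.

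**3. Size, as an illustration.** Simulation with 52 per arm, normal times, σ = 9.49 and a two-sided test at 0.05. Each infant has a latent exit score with correlation ρ to feeding time, and exits when the score passes the cut-off that gives the arm's exit rate. Exit rates and ρ are assumptions; the article gives neither.

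| True difference (days) | Exits control / massage | ρ | Mean difference among achievers (days) | t-test rejection |
|---|---|---|---|---|
| 5.2 | none | – | 5.2 | 0.78–0.79 |
| 5.2 | 15% / 5% | 0.7 | 4.1 | 0.60 |
| 5.2 | 20% / 5% | 0.7 | 3.6 | 0.48–0.49 |
| 5.2 | 15% / 5% | 0.3 | 4.7 | 0.67–0.68 |
| 5.2 | 15% / 5% | 0 | 5.2 | 0.74–0.75 |
| 5.2 | 20% / 20% | 0.7 | about 5.2 | 0.78 |
| 0 | 5% / 20% | 0.7 | 1.6 in favour of massage | 0.13–0.15 |
| 0 | 20% / 20% | 0.7 | 0 | about 0.05 |

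As an extreme, suppose exactly the slowest infants exit, at 10% in control and 30% under massage, with no true difference. The spurious benefit is then 2.2 days (σ = 7.26) to 2.9 days (σ = 9.49), and the t-test rejects about 40% of the time.

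**4. Worst-rank Wilcoxon on all 104 infants.** With a true 5.2 days and no exits its power is about 0.76. At 15% / 5% and ρ = 0.7 it is 0.78–0.79, against 0.60 for the t-test among achievers. In the extreme case above it rejects 8.5–8.7%. There, more massage infants share the worst rank, so the test is picking up the real excess of failures and leans against massage.

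Balanced exits cost power. At 20% in each arm it falls to 0.61 if exactly the slowest exit, and to about 0.46 in my run at ρ = 0.7.

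**The case against.** Several points stand.

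- **Removal of every non-achiever is an inference.** A reader might infer that the plan deletes all infants who exit and runs a t-test on the successes. The documents do not say that. Table 1 defines no analysis set, and the exclusion sentence concerns the intervention, a 7-day course, while expected time to full feeds is about 28 to 34 days. An infant who completes the course and exits later has not clearly discontinued anything. Nor is the t-test the only test named. Equally, the article does not say that infants who die will have a feeding day imputed.
- **Not every exit is a treatment failure.** Discharge before full feeds may be unrelated to feeding, and no reasons are given. Entry requires clinical stability and excludes sepsis and necrotizing enterocolitis, so deaths may be few.
- **Bias is not automatic.** Equal exits, or exits unrelated to feeding, leave the estimate at about 5.2 days. Of the 18 to 19 points of power lost at 15% / 5%, about 5 are plain loss of numbers, which the 20% allowance already anticipates.
- **An unseen analysis plan may hold the detail.** That excuses missing detail on censoring. It does not excuse an outcome-dependent exit rule, an exclusion sentence and an imputation sentence that the article does state and that give these infants no valid value.

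**Conclusion.** The point holds as a defect in how the stated rules fit together. The article defines an outcome that only achievers have, makes non-achievement an exit, and offers exclusion or imputation, neither of which protects the randomised comparison when exits are unequal and related to slow feeding. The direction of any bias is unknown. Under the assumed inputs it runs from a loss of about 1.1 days (5.2 to 4.1, at 15% / 5%) to a spurious gain of about 1.6 days (no true difference, 5% / 20%), and is nil when exits are balanced or non-informative. These sizes rest on assumed exit rates, ρ = 0.7 and a back-solved σ of 9.49. The structural conclusion does not depend on them. Because it concerns the primary result, it should be settled before unblinding.

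**What to change.** Reconcile Table 1 with sections 3.11 and 3.12, and state that exit from the trial does not mean exit from the analysis. Then fix one primary analysis of all randomised infants:

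- **Preferred:** the planned Wilcoxon test, stratified by birth weight, with infants who die or leave without reaching full feeds ranked worst.
- **Alternative:** cumulative incidence of full feeds with death as a competing event. Early discharge may be informative, so simply censoring it is not enough. Add a sensitivity analysis that counts discharge before full feeds as non-achievement.

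In either case, do not impute feeding times after death, and report deaths and non-achievers by arm, with reasons for early discharge.

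**Cost.** No new assessments are needed during the stay, and the preferred option stays within the planned family of tests. Recruitment was still open when the article was written. The main result becomes a rank or cumulative-incidence result instead of a mean difference, which departs from the two-means basis of the sample size, so power should be restated. Some discharges unrelated to feeding will be ranked as failures. If exits are frequent and balanced, power falls: from about 0.76 to between 0.46 and 0.61 at 20% in each arm under the assumptions above, and less at lower rates.
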